**Primary outcome measure:**	
	Oswestry Disability Index (ODI)
**Secondary measures:**	
a.	Rowland Morris Instrument (0–24 scale of disability)
b.	VAS Pain score (0–10)
c.	Physical activity levels (objectively measured using accelerometers)
d.	Functional evaluation including strength when pushing (peak and average kg of force)
e.	Functional evaluation including strength when pulling (peak and average kg of force)
f.	Comfortable (up to maximum baseline pain level) range of motion in flexion (degrees from neutral)
g.	Comfortable (up to maximum baseline pain level) range of motion in extension (degrees from neutral)
h.	Duration of time sitting comfortably (up to maximum baseline pain level) (minutes)
i.	Duration of time standing comfortably (up to maximum baseline pain level) (minutes)
j.	Duration and distance walking comfortably (up to maximum baseline pain level) (minutes and meters)
k.	Summed VAS pain × days rating
l.	Days of impairment (days)
m.	Lost workdays (days)
n.	Time to exacerbation (days until increase 3/10 pain)
o.	Rescue acetaminophen tablets consumed (% and number)
p.	NSAID discontinuation (%)
q.	Opioid discontinuation (%)

Functional assessments will be completed using a standardized protocol on a BTE EvalTech system. Standard protocols for Lumbar Flexion/Extension, Lumbar Lateral Flexion, Shoulder Height Push and Pull, Cart Height Push and Pull are used. Researchers performing assessments are trained to perform all assessments exactly the same following the BTE EvalTtech protocol (Figure 2).

**Figure 2 F2:**
[figure not shown]
Shoulder height push assessment using BTE EvalTech system.

Subjective outcomes data will be collected using computerized data collection tools utilizing Filemaker Pro™ database management to assure complete and accurate data collection. Data will be collected at enrollment and subsequent treatments. Data after treatments end will be collected in person using the same tools for every participant study by a blinded assessor.

### Assessments

Timing of assessments is identical in each arm. Assessments will be conducted by blinded assessors. Enrollment, randomization and initial treatment will occur at the time of enrollment. All participants will return 1 week after initial treatment for assessment of subject ability to correctly use their assigned device; have questions answered about the protocol, and to complete week 1 assessment. Subjective assessments will be measured at baseline, 1 week, 4 weeks, 8 weeks, and 12 weeks. Objective assessments will be measured pre and post-treatment at baseline and post-treatment at week 1, week 4, and week 12. No treatments are provided by the researchers after week 1, although patients will be performing home treatments per protocol for the entire 12 week period. Compliance will be assessed using digital time data logs recorded automatically by each device and diaries kept by participants. Participants in each arm will have identical and comparable contact time with providers and assessors to minimize treatment bias. All participants will be contacted weekly by a blinded assessor via telephone to encourage compliance and use of daily treatment diaries.

At each assessment, all participants receive the same assessment, including questionnaire, physical functioning assessment form, and recording of accelerometer use. All measures will be assessed using computerized data collection methods at baseline and each follow-up, except at the 8-week follow-up where outcomes will be assessed over the phone. There are four objective measures which are assessed via electronic device (Actigraph GT3X + Accelerometers and EvalTech functional testing equipment manufactured by BTE Technologies). The accelerometers provide physical activity levels on a per minute basis and store up to 40 days of data. These accelerometers have demonstrated validity and reliability in a variety of settings [30-38]. Functional strength and lumbar range of motion will be captured using EvalTech functional evaluation tools. These include fully modifiable load cells allowing different heights, widths, and orientations, as well as electronic range of motion devices for adequate capture. All trials will be performed 3 times. Pushing and pulling strength will be three trials each with exertions for 5 seconds and a 20 second break between trials. These will be at both shoulder height and cart height (approximately 49 inches). There will be a minimum of 6 trials (3 push and 3 pull at both shoulder height and cart height). Peak and average forces will be recorded for each trial.

### Treatment protocols

Subjects will be allocated to one of the three arms. Each treatment arm will have identical numbers of visits and contact time. Each arm will receive the uniform instructions for using of their assigned electrotherapy device. Patients will be instructed to use their assigned device daily upon waking and before bedtime, and up to two additional treatments during the day as needed (e.g., 4 1-hour treatment sessions). Providers will place electrodes and activate the device as per the protocol for each arm. Patients will be told that it is possible to not immediately feel effects of electrical treatment due to current levels that do not meet sensory thresholds. Patients will return after 1 week for reevaluation on electrode placement and ability to achieve the required self-administered stimulation levels. Providers are trained in standardized fashion to educate each participant on their assigned therapy.

The H-Wave® device delivers electrical stimulation through the placement of 4 electrode pads in a rectangular geometric pattern at the circumference of the low back pain nidus. Patients will be instructed on optimal electrode placement for home use. The H-Wave® Device is controlled by the patient after instruction from a therapist or practitioner. The stimulation parameters in terms of pulse duration and frequency are proprietary for the manufacturer and thus are not included in this protocol. However, the maximal intensity offered by the device is the goal of the treatment intensity. Patients are instructed to achieve the highest intensity possible in graduated fashion. Lower intensities are accepted if the patient cannot comfortably reach the maximal device intensity and will be noted on diary logs. There are controls for intensity and frequency, which the patient manipulates according to specific instructions and tolerances. Patients in this arm will be required to reach near maximal intensity on low frequency. The maximal intensity may, in rare cases, induce transient muscular contractions. Patients are instructed not to increase the intensity to a painful level. The treatment is then self-administered for the duration of the study.

There are no accepted standardized protocols found in the literature for TENs treatment of chronic low back pain. There are no trials that demonstrate maximum efficacy of pulse duration, wave type, or frequency. Therefore, the TENS units in this study allow adjustment of amplitude (intensity) only at a fixed frequency of 100 Hz with steady state pulsing. Modulation and pulse modes will be disabled in order to maintain uniformity of electrotherapy protocols. Pad placement will be directed by the provider to provide maximal clinical efficacy. The device is two channel TENS and will be administered by the patient after training by the provider.

The sham or control device will appear to operate in the same exact way as a fully functional TENS device, including battery drain and usage log. Subtherapeutic electrical current will be flowing to the pads so that the patient may perceive it as an active therapy. They will be instructed to use the device for the same duration as active treatments, daily upon waking and before bedtime, and up to two additional treatments during the day as needed (e.g., 4 1-hour treatment sessions). There is no quality evidence that subtherapeutic electrical current provides any clinical benefit over no electrotherapy effectiveness for LBP, however this will likely blind the patients because none of them have ever experienced the H-Wave Device. Blinding of patients is achieved as none will have previously experienced H-Wave, home based TENS therapy, or subtherapeutic electrotherapy. Further, patients are kept blind as to which electrotherapy devices out of the myriad devices on the market, are included in the study and therefore have few preconceived notions to their assigned device.

### Compliance

Compliance will be assessed by device logs and diaries. Each device will be capable of recording treatment applications and duration, and will be downloaded electronically at each in-person assessment. Total treatment time of 3.5 hours per week will be set as the threshold for compliance. If VAS Pain drops to a daily average of less than or equal to 2 out of 10, patients will be considered in compliance regardless of the number of treatments completed on that day. Patients will be called once per week to promote compliance and answer any questions.

### Discontinuation

Subjects will be encouraged to continue to follow-up throughout the study. There are no penalties for early dropouts other than the amount of incentive earned is reduced if the entire follow-up period is not completed. Each device (H-Wave®, TENS) has very low adverse effect profile. Although unexpected, those developing an adverse event will be reported to the IRB.

### Usual care and co-interventions

Study participants will be asked to avoid significant changes in medical/healthcare management of their LBP during the study period. All participants will be allowed to pursue usual care with their own personal treating physician. No other treatment other than the assigned electrotherapy intervention will be provided by the trial researchers. Usual care will be limited to non-invasive therapies, including medications such as NSAIDS (prescription or over the counter) and opioids, physical therapy, manipulation, stretching and aerobic exercise. Self-applications of heat or ice are also acceptable. All usual care medications and interventions will be recorded.

### Interventions not allowed

Any lumbosacral invasive procedure such as discectomy, microdiscetomy, laminectomy, lumbar fusion, disc desiccation by any chemical or thermal means. No injections into the lumbosacral area other than localized trigger point without the use of glucocorticoids. No other electrical therapies (PENS, Interferential therapy). No use of oral or systemic glucocorticosteroids. TENS and H-Wave® are not allowed except in the arms assigned to those treatments. Patients are asked about any additional treatments received at each assessment to determine continued eligibility.

### Statistical approach

#### Statistical power/Sample size

Sample size determination is based on the comparisons of the study arms for the primary outcome variable, ODI. In previous studies of low back pain patients , the baseline ODI values for one study group were mean (SD) of 60.2 (15.0) and for a second study group were 59.9 (14.4) [39,40]. The total score for the ODI is a percentage, ranging from 0 to 100. It is suggested that the reliability of the ODI requires a minimum detectable change of at least 10 points, as any smaller difference may be attributable to error in the measurement [25]. Assuming equality of the study arms at baseline, which can be assured by adjusting for baseline ODI in the regression model, and a minimal detectable effect size of a 10 point difference on the post-treatment value, sample size is based on a comparison of mean (SD) of 60 (15) vs. 50 (15), a 17% relative difference post treatment, using a two-sided comparison with alpha of 0.025 to allow for multiplicity adjustment. Under these assumptions, a sample size of n = 43 subjects per study arm is required to achieve 80% power. However, it is expected that the stimulation arms will produce at least a 25% relative improvement over the control arm. Assuming 60 (15) vs. 45 (15), a 25% relative difference, using a two-sided alpha 0.025 comparison, a sample size of n = 20 subjects per study arm is required for 80% power, or n = 25 subjects for 90% power. Allowing for a 20% dropout rate, a sample size of n = 38 subjects will be enrolled in each study arm to provide n = 25 evaluable subjects for data analysis.

### Statistical analysis

#### Primary analysis

The primary analysis is the comparison of the three study arms on the primary outcome, Oswestry Disability Index (ODI). Given that repeated measurements are collected, a mixed effects linear regression model will be fitted with an unstructured covariance matrix to account for lack of independence introduced by the repeated measurements. In this model, the repeated measurements are nested within study subject (weeks 0, or baseline, and weeks 1, 4, 8, and 12). The primary predictor is study group. A time variable will be included as a covariate, since visits will not always be at the planned intervals. Other covariates will be assessed for possible confounding in the relationship between treatment arm and outcome. It is likely that the pattern of dropouts will vary between the study groups, where the study interventions that are most effective having the dropouts later on in the follow-up, while the intervention least effective to have dropouts early on. The analysis will emphasize the 4-week time point as the primary end point, which ends the intensive intervention period. At 4 weeks compliance to the protocol and complete follow-up should be at a maximum. The remaining time to 12 weeks will measure long term effectiveness and acceptance of the study interventions.

#### Secondary analyses

The changes from baseline to each follow-up visit in the pain VAS (the main secondary endpoint) will be analyzed using the same longitudinal model described above for the Oswestry score. Key secondary comparisons will include the three pair wise comparisons between the treatment groups in the mean change in the Roland Morris Instrument, VAS, strength, and flexibility measures at the different time points.,

The changes to 12 weeks will evaluate the persistence of treatment effects of the interventions to that time; changes to 4 weeks evaluate treatment effects at the completion of the intensive intervention period, and the slopes from weeks 4 to 12 evaluate changes in the treatment effects after 4 weeks. The null hypothesis is that there is no difference between the three treatment arms at 12 weeks.

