#### Co-variates

Age, gender, tobacco, undiagnosed anxiety, undiagnosed depression, past back pain history, prior and current NSAID use, rescue acetaminophen use.

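### The main secondary analysis sends change from baseline in pain VAS to a model that has week 0 as a response and names no baseline VAS covariate; response and baseline handling need to be fixed

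*Protocol article*

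**What the plan says.** The Secondary analyses section of the protocol article defines the response and the model in one sentence: "The changes from baseline to each follow-up visit in the pain VAS (the main secondary endpoint) will be analyzed using the same longitudinal model" as the Oswestry score. It then asks for pairwise group comparisons of mean change in Roland Morris, VAS, strength and flexibility at the various visits.

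The model referred to is in Primary analysis. There, "a mixed effects linear regression model will be fitted with an unstructured covariance matrix", and "the repeated measurements are nested within study subject (weeks 0, or baseline, and weeks 1, 4, 8, and 12"). Its definite predictors are given as: "The primary predictor is study group. A time variable will be included as a covariate". Other covariates are only to be assessed for confounding.

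Baseline adjustment appears once, under Statistical power/Sample size, and for the ODI only: equality of the arms at baseline is something "which can be assured by adjusting for baseline ODI in the regression model". The Co-variates section reads: "Age, gender, tobacco, undiagnosed anxiety, undiagnosed depression, past back pain history, prior and current NSAID use, rescue acetaminophen use". Neither baseline VAS nor baseline ODI is in that list.

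**The concern.** The two sections do not fit together. A change from baseline has no value at week 0 other than zero, yet the model it is assigned to has week 0 as one of five responses. An analyst must alter one of them: drop week 0, replace changes by VAS levels, or add terms that are not stated. These repairs do not all give the same estimate or the same precision, and the text does not choose between them.

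Most of the available repairs also make no proper use of baseline VAS. The article itself calls this the main secondary endpoint, and each arm enrols only 38 patients. Baseline VAS is collected from everyone, so precision would be lost for no reason and chance differences at baseline would pass into the result.

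**Working it through.** **The plan's own figures.** The article gives no figure for the VAS analysis. Its ODI sample sizes reproduce with n = 2(z₁ + z₂)²·SD²/d², SD 15, two-sided alpha 0.025: 43 per arm for 10 points at 80% power, and 20 and 25 per arm for 15 points at 80% and 90%. They do not bear on this point.

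**Reading 1: a change row at week 0.** Let S be the 5x5 covariance of VAS levels and C the matrix that subtracts baseline from each visit. The covariance of the changes is C S Cᵀ. With assumed exchangeable correlations of 0.3, 0.5 and 0.7, the week-0 variance is 0, the rank is 4 of 5 and the determinant is 0. Without week 0, the 4x4 matrix has full rank 4.

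**Reading 2: changes at weeks 1, 4, 8 and 12 only.** This can be fitted, but it is an unadjusted change score. With b the baseline, f the follow-up and β the slope of f on b:

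Var(f − b) = Var(f given b) + (1 − β)²·Var(b)

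The second term is what adjustment removes. The article gives no VAS variance, so the following are assumptions: scale 0-10, mean 6 and SD 1.8 before selection, values clipped to the scale, and test-retest reliability 0.4 to 0.7. The cut at 5 or more is the article's entry criterion. Simulating 2 million patients per case gives a baseline SD of 1.24 after selection (variance 1.54), and:

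| Reliability | β | Adjusted variance | Change-score variance | SE ratio |
|---|---|---|---|---|
| 0.4 | 0.40 | 2.64 | 2.64 + 0.60² × 1.54 = 3.19 | √(3.19/2.64) = 1.10 |
| 0.7 | 0.70 | 1.61 | 1.61 + 0.30² × 1.54 = 1.75 | √(1.75/1.61) = 1.04 |

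The loss of effective sample is 1 − 2.64/3.19 = 17% and 1 − 1.61/1.75 = 8%.

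Sensitivity: with equal SDs at all visits and no truncation, the variance ratio is 2(1 − ρ)/(1 − ρ²) = 2/(1 + ρ). That is 1.54, 1.33 and 1.18 at ρ = 0.3, 0.5 and 0.7, so the SE would be 24%, 15% and 8% larger. The entry cut narrows baseline and so reduces the penalty. The 4% to 10% range is the more cautious one.

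Chance imbalance: each point of baseline difference between arms shifts the unadjusted estimate by 1 − β, about 0.3 to 0.6 points. With an assumed baseline SD of 1.3 and 30 per arm (38 × 0.8 = 30.4), the SE of the baseline difference is 1.3·√(2/30) = 0.34. A typical shift is therefore 0.34 × 0.3 = 0.1 to 0.34 × 0.6 = 0.2 points.

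**Reading 3: VAS levels at weeks 0 to 12, changes as contrasts.**
- *With only the stated predictors.* A single group coefficient averages the week-0 difference, which is null by design, with the follow-up differences. Its expectation is (1ᵀS⁻¹d)/(1ᵀS⁻¹1), with d = (0, −1.5, −1.5, −1.5, −1.5) as an assumed effect. With SD 1.3 at baseline and 2.2 afterwards, it is −0.55, −0.21 and +0.33 at correlations 0.3, 0.5 and 0.7. With equal SDs it is −1.2.
- *With group-by-visit terms and free baseline means.* On complete data the fitted means are the sample means, so the week-4 contrast equals the change-score contrast. In one simulated data set with 38 per arm both were −18.14 (on a 0-100 scale). This returns to the unadjusted change score of Reading 2.
- *With group-by-visit terms and baseline means set equal across arms.* This does use baseline VAS, but it is not stated.

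**The case against.** The strongest reply is that the sentence limits itself to changes to follow-up visits, so it never creates a week-0 change. That is right. A reader might infer that the analysis will fail to converge or will give a meaningless coefficient; the article does not support this. A constant row would show up at once and a competent analyst would remove it. One might also give week 0 a small artificial variance and show the group estimate shrinking towards zero. That result would come from the invented variance and the missing group-by-visit term, and it says nothing about the analysis intended here.

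A second reply is that VAS levels with visit-specific contrasts fit both sections, and that the stated interest in changes to 4 and 12 weeks and in slopes points that way. This is a legitimate model and would resolve the conflict. It needs a group-by-visit term that Primary analysis does not list, however, and it improves on the raw change score only if the baseline means are constrained.

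Third, the covariate list also leaves out baseline ODI, which the sample-size section says is adjusted for, so adjustment for baseline VAS may be meant by analogy. That is possible but not stated. If week 0 stays a response, baseline would then be both outcome and covariate.

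Finally, an article may leave such detail to an analysis plan that is not shown. Silence alone would be no finding. What remains is that two stated elements, the response and the model, do not match.

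**Conclusion.** The point holds as a specification conflict with a modest, avoidable cost. The response named for the main secondary analysis does not fit the model it is assigned to, and baseline VAS has no stated role. On the natural reading the result is an unadjusted change score. It is unbiased under randomisation, with an SE about 4% to 10% larger than a baseline-adjusted analysis, equivalent to about 8% to 17% of the sample. It also passes on chance imbalance, typically 0.1 to 0.2 VAS points.

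These sizes rest on an assumed 0-10 scale (the article gives 0-100 in the Outcome measures text and 0-10 in Table 1; the SE ratio does not depend on the unit), entry at 5 or more, a pre-selection mean of 6 and SD of 1.8, and reliability 0.7 to 0.4. The singularity belongs only to a reading that adds a week-0 change row.

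**What to change.** Replace the sentence in Secondary analyses with, for example: *Pain VAS (or its change from baseline) at weeks 1, 4, 8 and 12 is the response; baseline VAS is a fixed covariate and week 0 is not a response; group, visit and group-by-visit are fixed effects, with an unstructured 4x4 covariance.* With baseline as a covariate, level and change give the same group differences.

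A practically equivalent choice is VAS levels at weeks 0 to 12 with group-by-visit terms and baseline means constrained equal across arms. Either resolves the point, and one should be named. Because VAS is recorded before and after treatment at week 0, state that baseline is the pre-treatment value.

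Use the same form for Roland Morris, strength and flexibility, each with its own baseline and its own visits (the Assessments section schedules objective measures at weeks 1, 4 and 12, not 8).

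The cost is wording only. Baseline values are already collected, and no extra data or patients are needed.

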### Outcome measures

Outcome measures will be assessed at baseline, 1 week, 4 weeks, 8 weeks, and 12 weeks, with the primary outcome being at 4 weeks. Assessment will occur in the same manner and at the same time intervals for all treatment arms utilizing standardized methods. Treatment failure will be defined as if patient terminates assigned treatment arm for non-efficacy or election to pursue surgical or invasive procedure or other excluded cointerventions.

The primary outcome measure will be the Oswestry Disability Index (ODI). The ODI is widely used in low back pain intervention trials, and provides a measure of functional improvement The ODI was selected compared to a subjective pain rating [25-29]. Secondary outcome measures include Rowland Morris Instrument (0–24 scale of disability); VAS Pain score (0–100); physical activity levels objectively measured using accelerometers worn by participants during waking hours over during the entire 12 week study period; functional capacity evaluation including strength when pushing and pulling (3 repetitions lasting 5 seconds each of both pushing and pulling measuring both peak and average kg of force according to standard EvalTech Functional Systems protocol which utilizes a load cell to measure forces exerted); range of lumbar spine motion (up to participants maximum range of specific movement) in flexion, extension, lateral rotation; duration of time (minutes) sitting comfortably (subjective estimate made by participant during questionnaire); duration of time (minutes) standing comfortably (subjective estimate made by participant during questionnaire); duration (minutes) and distance (meters) walking comfortably (subjective estimate made by participant during questionnaire); summed VAS pain × days rating; days of impairment (days); lost workdays (days); time to exacerbation (days until increase 3/10 pain); rescue acetaminophen tablets consumed (% and number); NSAID discontinuation (%); opioid discontinuation (%). The pain VAS score is assessed immediately before and after treatment at weeks 0, 1, and daily scores pre and post home-treatment in a diary that the participant keeps (Table 1).

**Table 1 T1:** Outcome measures

	

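### The key secondary contrasts are defined as differences in mean change with no stated adjustment for each outcome's own baseline; adding that term is a nearly free gain in precision

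*Protocol article*

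**What the plan says.** Under Secondary analyses, the change in pain VAS "will be analyzed using the same longitudinal model described above for the Oswestry score". The next sentence defines the key secondary comparisons as "the three pair wise comparisons between the treatment groups in the mean change in the Roland Morris Instrument, VAS, strength, and flexibility measures". These are to be made at several visits. The sentence names no model and no baseline term.

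Three other places bear on the point:

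- **Statistical power/Sample size** assumes the arms are equal at baseline, "which can be assured by adjusting for baseline ODI in the regression model". This is the only mention of adjusting for a baseline outcome value, and it concerns the ODI alone.
- **Primary analysis** describes the ODI model as one in which "the repeated measurements are nested within study subject (weeks 0, or baseline, and weeks 1, 4, 8, and 12"). Week 0 is therefore one of the responses.
- **Co-variates** lists "Age, gender, tobacco, undiagnosed anxiety, undiagnosed depression, past back pain history, prior and current NSAID use, rescue acetaminophen use". No baseline outcome value is on the list.

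The data needed are collected: "Outcome measures will be assessed at baseline, 1 week, 4 weeks, 8 weeks, and 12 weeks". The Assessments section qualifies this for the objective measures. They are taken before and after treatment at baseline, then after treatment at weeks 1, 4 and 12. Week 8 is a telephone contact.

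**The concern.** Subtracting baseline is not the same as adjusting for it. A change score fixes the coefficient of baseline at 1. A regression on baseline estimates that coefficient, which with equal SDs is the correlation r between baseline and follow-up. When r is below 1, the change score over-corrects a baseline difference and adds noise. When r is below 0.5, it is less precise than ignoring baseline altogether.

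The arms are small: 38 enrolled, about 30 left after the planned 20% dropout, and 25 evaluable on the article's own statement. Randomization is stratified by opioid use and workers' compensation claim, not by any baseline score. A chance difference in baseline Roland Morris, VAS, strength or flexibility is therefore to be expected in some of the three arm pairs. The Discussion says that a randomization failure cannot be overcome, yet an imbalance in a measured baseline can largely be dealt with by adjusting for it. At stake are wider confidence intervals than the data allow, and secondary estimates that move with that imbalance.

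**Working it through.** **1. The plan's own figures.** The only sample sizes stated are for the ODI. With the normal approximation, n per arm = 2(z for two-sided alpha 0.025 + z for power)² × (SD/difference)²:

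- 10 points, SD 15, 80% power: 2 × (2.241 + 0.842)² × 2.25 = 42.8, so 43.
- 15 points, SD 15, 80% power: 2 × (2.241 + 0.842)² × 1 = 19.0, so 20 when rounded up.
- 15 points, SD 15, 90% power: 2 × (2.241 + 1.282)² × 1 = 24.8, so 25.

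All three match the article. They do not bear on the secondary contrasts, for which no power is stated.

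**2. Would the ODI model supply the adjustment?** Take a mixed model with week 0 among the responses, a free mean for each arm at each visit, an unstructured covariance and complete data. The estimated means are then the sample means. The arm difference in change from week 0 is (follow-up mean minus baseline mean) in one arm less the same quantity in the other, which is the change-score difference. Baseline adjustment arises only if baseline enters as a covariate or the week-0 means are constrained equal across arms. The article states neither.

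**3. Variance.** Let both visits have SD s and correlation r, with n per arm.

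- Change score: variance per patient 2s²(1-r).
- Baseline-adjusted: s²(1-r²), with the slope treated as known.
- Ratio: 2(1-r)/[(1-r)(1+r)] = 2/(1+r), whatever the value of n.

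**4. Chance imbalance.** If the arms differ at baseline by d, the expected change-score estimate is the true effect minus (1-r)d. The SD of d at n = 30 (38 × 0.8 = 30.4) is √(2/30) = 0.26 baseline SDs.

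**5. Results.** The documents give no r, so the range is assumed. The power column also assumes an effect of 0.667 SD (the ODI ratio 10/15, borrowed for illustration), two-sided alpha 0.05 and 30 per arm.

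| r | Variance ratio 2/(1+r) | Adjusted patients equivalent to 30 on change, 30(1+r)/2 | Shift from a 0.26 SD imbalance, in SD | Power, change vs adjusted |
|---|---|---|---|---|
| 0.3 | 1.54 | 19.5 | 0.18 | 59% vs 77% |
| 0.5 | 1.33 | 22.5 | 0.13 | 73% vs 85% |
| 0.7 | 1.18 | 25.5 | 0.08 | 92% vs 95% |
| 0.8 | 1.11 | 27.0 | 0.05 | 98% vs 99% |

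**6. Check by simulation.** In 20,000 simulated two-arm trials at r = 0.5 and 30 per arm, the adjusted-to-change variance ratio was 0.776, against 0.75 from the formula. The gain is slightly smaller in small samples, where the slope must be estimated. The estimate moved by -0.49 per unit of baseline difference without adjustment, and by 0.01 with it.

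**The case against.** The strongest reply is that the article never calls these comparisons raw or unadjusted. Mean change is a quantity to be estimated, and a model with a baseline covariate estimates it too. VAS stands in the same sentence as Roland Morris, strength and flexibility, and the sentence before sends VAS change to the longitudinal model. The second sentence may therefore list contrasts to report rather than prescribe a separate method. The covariate list proves little, since it also omits baseline ODI, for which adjustment is mentioned elsewhere. The form of a secondary model is a detail that an article may leave to the full protocol or analysis plan.

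Most of this stands. A reader might infer that the plan prescribes an unadjusted analysis for Roland Morris, strength and flexibility and protects only VAS. The text supports neither half. The first is an inference from silence, and the second credits the ODI model with an adjustment that its description does not contain.

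What survives is narrower. The article fixes the quantity and the contrasts, invokes baseline adjustment for one outcome only, and describes a model that does not provide it unless one more feature is specified. The clarification is needed under either reading. It is also fair that the size rests on an assumed r, equal SDs and an illustrative effect.

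**Conclusion.** The point holds as a low-cost improvement to the key secondary analyses. As described, the contrasts for Roland Morris, VAS, strength and flexibility carry no stated baseline adjustment and would in effect be change-score differences, whether computed directly or from the ODI model with free week-0 means and complete data. The cost is a variance 11% to 54% larger over assumed r of 0.8 down to 0.3, with equal SDs at both visits and slightly less to gain in small samples. A chance baseline difference is carried into the estimate at (1-r) of its size.

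A reader might take this to mean that the secondary results would be biased. They would not be on average, because randomization makes the expected baseline difference zero. The harm is lost precision, and sensitivity to whatever imbalance occurs in this one trial. It is small when r is 0.8 or more. The ODI sample-size figures are not affected.

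**What to change.** State under Secondary analyses that the model for each of these outcomes includes the baseline value of that same outcome as a covariate, or constrains the baseline means to be equal across arms. Apply this at each time point where the outcome is measured, noting that the objective measures have no week-8 value. Report the three pairwise baseline-adjusted differences with confidence intervals. Unadjusted mean changes can still be tabulated descriptively. With baseline as a covariate, the arm difference is the same whether the response is the follow-up value or the change, so the stated quantity is kept.

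For strength and range of motion, name in advance which of the two baseline readings is used. VAS needs the same choice, since Outcome measures has it recorded before and after treatment at week 0. A reading taken after the first treatment follows allocation and may already contain some treatment effect, which weakens it as a covariate and undermines an equal-means constraint.

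The cost is a few sentences of text, with no new data, visits or patients.
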